##### Downstream costs

Both EBPs may lead to changes in VA healthcare use. We will consider all non-intervention-related healthcare use as downstream (VA outpatient, pharmacy, and inpatient care). Costs of this downstream utilization will be captured using the VA MCA.

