### Medications for Addiction Treatment (MAT)

Medications for Alcohol Use Disorder (MAUD) and Medications for Opioid Use Disorder (MOUD) are implementation priorities within VA primary care and mental health but have not been systematically incorporated in HUD-VASH. MAUD includes naltrexone and acamprosate. Across meta-analyses and systematic reviews, MAUD resulted in significantly decreased alcohol consumption compared to placebo [16, 17]. In a meta-analysis [16] of 118 randomized controlled trials (RCT), the number needed to treat (NNT) to prevent return to drinking was 11 for acamprosate and 18 for oral naltrexone. Injectable naltrexone was significantly associated with reduced drinking days (weighted mean difference [WMD] −5 days).

MOUD includes methadone, buprenorphine, and extended-release naltrexone. In a meta-analysis of 11 RCTs [18], methadone was significantly more effective than placebo or non-pharmacological treatments on treatment retention (risk ratio [RR] 4.44) and the reduction of morphine-positive urine or hair analysis (RR 0.66). In a meta-analysis of 31 RCTs, buprenorphine was significantly more effective than placebo on treatment retention at low (RR 1.5); medium (RR 1.74); and high (RR 1.82) doses. In an RCT [19] comparing extended-release naltrexone to counseling, relapse was significantly lower in the naltrexone group (43% vs. 64%) over 24 weeks. Buprenorphine and methadone significantly reduce mortality [20], opioid-related overdoses and acute care [21].

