##### Assessing MAT and CBT-SUD Costs as actually implemented

The predominant cost of delivering MAT and CBT-SUD in HUD-VASH programs is prescriber time and case manager time, respectively. We will use VA administrative data to identify visits in which MAT was prescribed or CBT-SUD was delivered. Interviews with HUD-VASH prescribers will be used to estimate minutes/visit spent on MAT; at implementation sites, we will add a mandated field to templated CBT-SUD notes that indicates time spent outside the encounter. We will multiply employee hourly wages by average time spent on each EBP. Data from 18-month HUD-VASH staff interviews will be used to glean contextual factors that may influence clinical and case manager activities.

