##### Budget impact analysis

We will also prepare a budget impact analysis (Table 4), characterizing the costs, cost offsets, and non-financial benefits of: MAT and CBT-SUD sustainment and spread in HUD-VASH; and REP vs. REP + CE. We will compare healthcare utilization costs between REP and REP + CE sites using a difference-in-differences research design. This will be performed using both the standard two-way fixed effect approach as well as with the Callaway and Sant’Anna [42] estimator, which takes into account staggered adoption. Our cost analyses will provide data about the magnitude and features of expected EBP costs and benefits. We will assess whether REP + CE yields a sufficient combination of downstream financial cost offsets and non-financial benefits to justify REP + CE vs. REP alone in spreading and sustaining MAT and CBT-SUD. We will also provide information about HUD-VASH site-level contextual factors that may signal an above-average benefit from using REP + CE (vs. REP alone).

**Table 4 Tab4:** Budget impact analysis

Expected resources (costs)		Expected benefits
**Implementation Strategy Costs**	**Care delivery costs**	**Cost offsets and non-financial benefits**
• *Fixed*: Implementation team, HUD-VASH and mental health staff time spent in EBP training • *Variable*: Staff time spent giving/receiving AD and/or CBT-SUD TA, implementation team time spent consulting with HUD-VASH peers, peer time spent delivering CE*	• HUD-VASH and mental health prescriber time spent delivering MAT • HUD-VASH staff time spent delivering CBT-SUD • Downstream healthcare use	• *Cost offset:* decreased use of VA housing services • *Non-financial benefits*: HEVs’ housing stability; improved HEVs’ care experiences; improved HUD-VASH team experiences providing care

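### As the cost categories are worded, MAT medication cost enters none of them; on the alternative reading, MAT visits are costed twice

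*Protocol article*

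**What the plan says.** All references are to the Protocol article, Economic evaluation.

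- **Delivery cost** (Assessing MAT and CBT-SUD Costs as actually implemented): the section opens by stating "The predominant cost of delivering MAT and CBT-SUD in HUD-VASH programs is prescriber time and case manager time, respectively". The only formula is "We will multiply employee hourly wages by average time spent on each EBP".
- **Strategy cost** (Costs of implementation strategies): time of the implementation team, academic detailers and peers.
- **Downstream cost** (Downstream costs): after a sentence saying that both EBPs may change healthcare use, the text reads "We will consider all non-intervention-related healthcare use as downstream (VA outpatient, pharmacy, and inpatient care". The source follows: "Costs of this downstream utilization will be captured using the VA MCA".
- **Table 4** (Budget impact analysis): the care delivery column has three lines. They are "HUD-VASH and mental health prescriber time spent delivering MAT", staff time for CBT-SUD, and downstream use.
- **Use of the costs** (Budget impact analysis): "We will compare healthcare utilization costs between REP and REP + CE sites using a difference-in-differences research design". The decision they serve is "We will assess whether REP + CE yields a sufficient combination of downstream financial cost offsets and non-financial benefits to justify REP + CE". The same section also promises the costs of sustaining and spreading MAT and CBT-SUD.

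**The concern.** CBT-SUD consists of staff time, so wages times time can represent its delivery cost. MAT also has a product: "MOUD includes methadone, buprenorphine, and extended-release naltrexone", and naltrexone and acamprosate for alcohol use disorder. A product cost needs a place in the accounting, and the stated rules give it none on their natural reading.

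Two results are exposed. The first is the budget impact of MAT sustainment and spread, which partners would use to plan national roll-out. It would be too low whichever strategy does better. The second is the judgement of REP + CE against REP. The missing cost grows with the number of Veterans on MAT, and MAT reach is among the trial's primary outcomes. The reach, adoption, housing and acute care results are not affected.

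**Working it through.** The article states no cost figure to reproduce, so the check traces MAT medication and MAT visits through each category under the two possible meanings of *intervention* in Downstream costs.

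| Category | Medication: intervention = the EBPs | Medication: intervention = REP, REP + CE | MAT visit: intervention = the EBPs | MAT visit: intervention = REP, REP + CE |
|---|---|---|---|---|
| Delivery (wage × time) | no | no | yes | yes |
| Implementation strategy | no | no | no | no |
| Downstream (VA MCA) | no | yes | no | yes |
| Times counted | 0 | 1 | 1 | 2 |

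Neither meaning counts both items exactly once.

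**Which meaning is natural.** The sentence just before the downstream definition has both EBPs as its subject, which points to MAT and CBT-SUD. Against that, the Housing stability section speaks of levels of intervention and means REP and REP + CE. The first meaning fits the local context better, but the second is possible.

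**Direction between strategies.** Let M1 and M0 be the numbers of Veterans on MAT at REP + CE and REP sites, c the medication cost and t the prescriber-time cost per treated Veteran, taken as equal in both groups.

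- EBP meaning: the REP + CE minus REP cost difference is too low by (M1 − M0) × c.
- Strategy meaning: it is too high by (M1 − M0) × t.
- If M1 = M0, neither error affects the contrast. Under the EBP meaning, the sustainment and spread budget still omits c for every treated Veteran.

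**Scale, for illustration only.** Sample size and power gives 7,908 Veterans, AUD in 53%, OUD in 16%, and detectable gains of 2.7 points (MAUD) and 6.6 points (MOUD). An equal split is assumed, and AUD/OUD overlap is ignored.

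- Veterans per strategy: 7,908 / 2 = 3,954
- MAUD: 3,954 × 0.53 × 0.027 = 56.6
- MOUD: 3,954 × 0.16 × 0.066 = 41.8
- Total: about 98 additional Veterans on MAT, relative to the period before CARE-VASH

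The article gives no drug price, visit count, visit length or wage. All of the following values are assumptions.

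- Medication at $100 to $5,000 per treated Veteran: 98.3 × $100 ≈ $9,800, and 98.3 × $5,000 ≈ $492,000, left out under the EBP meaning.
- Prescriber time from 4 visits × 15 min × $60/h = $60 to 12 visits × 30 min × $150/h = $900 per treated Veteran: 98.3 × $60 ≈ $5,900, and 98.3 × $900 ≈ $88,500, counted a second time under the strategy meaning.
- Medication as a share of medication plus time: from 100 / (100 + 900) = 10% to 5,000 / (5,000 + 60) = 99%.

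The count of 98 is a before–after quantity. It is not M1 − M0, because both groups receive REP for 18 months and gains due to REP occur in both.

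**The case against.** The strongest case on the other side has four parts.

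1. **The exclusion is inferred.** The article never says that MAT drugs are left out, names pharmacy as a captured category, and elsewhere uses *intervention* for the strategies. This stands as far as it goes: the text is ambiguous. It does not rescue the plan, because the reading that captures the drugs counts the prescribing visits twice.
2. **The between-strategy comparison is not limited to downstream use.** The difference-in-differences sentence speaks of healthcare utilization costs in general. If that means all MCA costs, the drugs are in. So are the MAT visits, and adding the delivery lines of Table 4 to that total repeats them.
3. **This is a condensed article, and *predominant* implies other components.** An itemised cost list could indeed be left to a fuller document, and the silence on dispensing and administration is no finding. The medication gap is different, because it follows from an exclusion rule and a delivery formula that the article itself states.
4. **The size is unknown.** This stands in full.

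A reader might infer that the comparison is biased toward REP + CE by construction, so that this strategy will look falsely cheap. The documents do not support that. The direction depends on which meaning was intended and on CE actually raising MAT use, which is a hypothesis. A reader might also take about 98 Veterans times a drug price as the bias between strategies. That would use detectable before–after differences as if they were a REP + CE versus REP effect. Charging each of them 180 days of drug would also assume full persistence, although Table 3 lists one prescription and 180-day use as separate measures.

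**Conclusion.** The point holds as a defect in how the cost categories are defined. On the natural reading, MAT medication cost is counted nowhere. The budget impact of MAT sustainment and spread is then understated, and REP + CE is understated relative to REP if it raises MAT use as hypothesised. On the other reading, the drugs are counted once and MAT visits twice, with the opposite effect on the comparison. The text needs correcting under either.

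No amount can be given. Under the assumed ranges, medication runs from 10% to 99% of medication plus prescriber time, so the omission could be minor or could dominate the cost of MAT. The conclusion rests on the stated definitions and on none of the assumed prices. It concerns the economic evaluation only.

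**What to change.** Make one of two changes.

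- Add MAT medication cost, taken from the VA MCA or pharmacy data, as a care delivery line in Assessing MAT and CBT-SUD Costs as actually implemented and in Table 4.
- Or state under Downstream costs that pharmacy includes MAT drugs.

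In either case, say what *intervention* means in that section. Exclude from downstream outpatient cost the MAT and CBT-SUD visits already costed as staff time. State that each cost enters once in the REP + CE versus REP comparison, including the difference-in-differences analysis.

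The cost is a few sentences and one more extract from a source already in use. Against the natural reading, the stated costs of MAT under both strategies will look less favourable.

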##### Budget impact analysis

We will also prepare a budget impact analysis (Table 4), characterizing the costs, cost offsets, and non-financial benefits of: MAT and CBT-SUD sustainment and spread in HUD-VASH; and REP vs. REP + CE. We will compare healthcare utilization costs between REP and REP + CE sites using a difference-in-differences research design. This will be performed using both the standard two-way fixed effect approach as well as with the Callaway and Sant’Anna [42] estimator, which takes into account staggered adoption. Our cost analyses will provide data about the magnitude and features of expected EBP costs and benefits. We will assess whether REP + CE yields a sufficient combination of downstream financial cost offsets and non-financial benefits to justify REP + CE vs. REP alone in spreading and sustaining MAT and CBT-SUD. We will also provide information about HUD-VASH site-level contextual factors that may signal an above-average benefit from using REP + CE (vs. REP alone).

**Table 4 Tab4:** Budget impact analysis

Expected resources (costs)		Expected benefits
**Implementation Strategy Costs**	**Care delivery costs**	**Cost offsets and non-financial benefits**
• *Fixed*: Implementation team, HUD-VASH and mental health staff time spent in EBP training • *Variable*: Staff time spent giving/receiving AD and/or CBT-SUD TA, implementation team time spent consulting with HUD-VASH peers, peer time spent delivering CE*	• HUD-VASH and mental health prescriber time spent delivering MAT • HUD-VASH staff time spent delivering CBT-SUD • Downstream healthcare use	• *Cost offset:* decreased use of VA housing services • *Non-financial benefits*: HEVs’ housing stability; improved HEVs’ care experiences; improved HUD-VASH team experiences providing care

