**Methods:**

We will use Replicating Effective Programs (REP) to implement MAT and CBT-SUD at 12 sites over 18 months. After 9 months of REP alone, half (n = 6) of these sites will also receive Consumer Engagement (CE) for 9 months, activating HEVs to adopt these practices via peer coaching. We will conduct a type 3 hybrid cluster-randomized trial to compare the impacts of REP versus REP + CE. Randomization will occur at two levels: implementation start date (3 cohorts) and the implementation strategy (REP versus REP + CE). We will use stratified block randomization to balance site size among sites receiving each strategy across cohorts. We will use mixed methods to assess the impacts of REP versus REP + CE on implementation outcomes (reach [primary outcome], adoption, and sustainment); Veteran outcomes (primarily housing); provider and Veteran experiences; and costs and budget impacts. We hypothesize that REP + CE will have higher implementation costs than REP but result in improved MAT and CBT-SUD implementation and Veteran outcomes, leading to a business case for REP + CE.

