## Methods

### Overview

We will conduct a cluster-randomized trial comparing sites (or clusters) randomized to REP versus REP + CE. Specifically, we will conduct a type 3 hybrid implementation-effectiveness trial [14] using a stepped wedge design with randomization at two levels: implementation start date (3 cohorts) and implementation strategy (REP vs. REP + CE). We will use stratified block randomization to balance site size among sites receiving each strategy across cohorts. We will use mixed methods to assess the impacts of REP vs. REP + CE. We hypothesize that REP + CE will have higher implementation costs than REP, but result in improved and more equitable EBP reach, adoption, sustainment, and housing outcomes, leading to a business case for REP + CE.

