### Study design

We plan a type 3 hybrid implementation-effectiveness trial [14], registered as NCT07141394 on 8/26/2025 and determined to be non-research by VA’s Central Institutional Review Board. We will use stratified block randomization, stratified by tertiles of each site’s number of HUD-VASH full-time equivalent (FTE) employees (proxy for size and resources).

Within the 12 sites, we will use a stepped wedge cluster randomized trial design [35] (Fig. 2) to study implementation outcomes, balanced for allocation to treatment timing and assignment to REP vs. REP + CE arms across 3 strata of 4 sites each (Fig. 3). Using a random number generator with assignment by our statistician, each stratum will be randomly assigned to 1 of 3 possible cohort pairings (cohorts 1 & 2; 2 & 3; 1 & 3). Within each stratum, 4 sites will be randomly assigned to 1 of the 2 cohorts in the pair, ensuring that there are early and late treatment timings within each stratum. Within each stratum-cohort combination (n = 2), the REP vs. REP + CE implementation strategy arm will be randomly assigned, and consent obtained thereafter. The staggering of sites into cohorts is necessary to provide HUD-VASH sites with optimal EBP and CE training within our resources. We selected the 9-month duration of REP, before augmenting with 9 months of CE at REP + CE sites, because we found this duration of REP to be effective in prior trials of a psychosocial EBP for HEVs [36]. We will be unable to blind sites (clusters) assigned to CE augmentation, as we need to engage with leadership regarding peer supports’ commitments. To optimize power in our effectiveness analyses, we will compare sites that receive REP vs. REP + CE vs. all other HUD-VASH sites in the nation that are not engaged in CARE-VASH.

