We will use a staggered adoption model [42], comparing reach and adoption pre-CARE-VASH, to REP alone, and to REP + CE. These models utilize fixed effects for sites to account for time-invariant confounders between sites as well as fixed effects for time-period to account for secular trends. We will implement this approach [42] using a doubly robust estimator based on stabilized inverse probability weighting [43], with weights based on HEV demographics and comorbidities (using the Multimorbidity-Weighted Index) [44]. The average treatment effect on the treated will be estimated based on comparison to the not-yet-treated periods and presented using an event-study approach which will estimate the intervention effect across time (i.e., for each quarter-year). In addition to providing intervention estimates for each quarter-year of the study, a pooled intervention effect estimate will be aggregated across the study period by taking weighted averages of the event-study estimates with non-parametric bootstrapping (1000 replications) used to provide standard errors for aggregated estimates. Sustainment will be compared between sites that received REP vs. REP + CE, with reach and adoption measures adjusted as described.

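### The REP + CE versus REP cost comparison does not limit controls to the same start cohort, so a cost effect of REP itself can enter the CE estimate

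*Protocol article*

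**What the plan says.** The Budget impact analysis section of the protocol article states: "We will compare healthcare utilization costs between REP and REP + CE sites using a difference-in-differences research design". On method it continues: "This will be performed using both the standard two-way fixed effect approach", together with the Callaway and Sant'Anna estimator, which it describes as handling staggered adoption. It gives no cohort-by-period term, no term for REP phase and no rule that controls come from the same cohort.

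The section on reach, adoption and sustainment cites the same staggered-adoption method. There the model has "fixed effects for time-period to account for secular trends", and effects are "estimated based on comparison to the not-yet-treated periods". Neither statement is repeated for costs.

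On the design, the abstract says: "We will use Replicating Effective Programs (REP) to implement MAT and CBT-SUD at 12 sites over 18 months". Sites start in three cohorts, and six of them add CE after 9 months of REP. The Study design section adds: "Within each stratum-cohort combination (n = 2), the REP vs. REP + CE implementation strategy arm will be randomly assigned". The Downstream costs section allows that both practices may change VA healthcare use.

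**The concern.** The contrast of interest is CE on top of REP. A difference-in-differences estimate of it needs controls whose costs would have moved as the CE sites' costs would have moved without CE. Here every site undergoes a second change, the start of REP, at one of three dates. When an early cohort adds CE, sites in a later cohort may be untreated or just starting REP. With period effects common to all cohorts, those sites help to form the counterfactual. If REP raises or lowers costs, part of that change is then credited to CE or taken from it.

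The estimate feeds the judgement whether cost offsets justify REP + CE over REP alone. The design already contains a comparison free of this problem: sites that started REP on the same date and were randomised against each other.

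**Working it through.** The article states no effect size, power or standard deviation for costs, so there is no figure of its own to reproduce. The check is a noise-free calculation of how much of a REP cost effect each estimator reports as CE.

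**Inputs from the article.** 12 sites in 3 cohorts of 4, with 2 REP and 2 REP + CE sites per cohort. CE begins at REP month 9 and lasts 9 months.

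**Assumptions.** The gap between cohorts is not in the text, so it was set to 3, 6, 9 and 12 months. Periods are quarters, with 12 months of pre-data and 0 or 9 months of data after cohort 3 ends. The true CE effect is 0 and the REP effect is 1 unit. The REP effect takes one of three lasting shapes: a step, a 9-month ramp or an 18-month ramp.

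**Hand example.** Take a 9-month gap, a step, CE start as the treatment date, and the nine CE months only. Cohort 2 starts REP exactly when cohort 1 starts CE, and cohort 3 starts REP when cohort 2 starts CE.

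- Never-CE controls (6 sites). For cohort 1, two of the six controls step up by 1, so the control change is 2/6 = 0.33. The CE sites, already on REP, change by 0. The estimate is 0 - 0.33 = -0.33. Cohort 2 gives -0.33 in the same way, and cohort 3 gives 0. Pooled: (-0.33 - 0.33 + 0)/3 = -0.22.
- Not-yet-CE sites added. Cohort 1 has 10 controls, of which 4 step up: -0.40. Cohort 2 has 8, of which 4 step up: -0.50. Cohort 3 gives 0. Pooled: -0.90/3 = -0.30.
- Same-cohort REP controls. CE and control sites share the REP path, so each cohort gives 0.

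**9-month gap, dated at CE start, 9 months of later data, all post-CE quarters, not-yet-CE controls:**

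| REP effect | Staggered estimator | Two-way model |
|---|---|---|
| Step | -0.41 | +0.01 |
| 9-month ramp | -0.35 | +0.13 |
| 18-month ramp | +0.02 | +0.19 |

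**Two-way model dated at REP start in the REP + CE arm, no later data:**

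| Gap | Step | 9-month ramp | 18-month ramp |
|---|---|---|---|
| 3 months | 0.24 | 0.08 | 0.02 |
| 6 months | 0.36 | 0.19 | 0.05 |
| 9 months | 0.42 | 0.28 | 0.10 |
| 12 months | 0.47 | 0.34 | 0.15 |

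**Ranges over gaps of 3 to 12 months and the three shapes:**

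- Two-way, dated at CE start: -0.04 to +0.28.
- Two-way, dated at REP start: +0.02 to +0.47.
- Staggered, dated at CE start: -0.44 to +0.20 over either follow-up window, and -0.30 to +0.20 on the nine CE months alone.
- Site effects plus cohort-by-quarter effects, or same-cohort REP controls: 0.000 throughout.

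The results are sensitive to shape. If the REP effect instead ends at month 18, the two-way leak is 0 when dated at CE start and reaches +0.62 when dated at REP start (12-month gap). Adding only a REP-on indicator to the two-way model removes the leak for a constant REP effect but not for ramps.

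**The case against.** The strongest reply is that the article fixes too little to be faulted. It gives no treatment date, control set or follow-up window for costs, and the not-yet-treated comparison belongs to the reach analysis. A full plan could date treatment at REP start, estimate each arm separately against not-yet-REP sites and contrast the arms within cohort; REP would then cancel. This stands as a limit on the size of the problem. It does not remove it. The standard two-way model is named outright and carries common period effects. The arm-by-arm route is not stated, and it would have not-yet-REP controls for only 0 to 4 of the 9 cohort-by-quarter CE cells at gaps of 3 to 12 months.

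A second reply is that the two-way model may have the smaller total error. In a simulation with assumed site-quarter noise (SD 1, autocorrelation 0.5), the estimator SDs were 0.37 for two-way and 0.42 within cohort. For a REP effect of 1 SD at a 9-month gap with an 18-month ramp, the two-way root mean squared error is sqrt(0.37² + 0.19²) = 0.42, no worse than the within-cohort contrast. At 2 SD it is sqrt(0.37² + 0.38²) = 0.53. The documents give no basis for either effect size, so this cannot settle the choice.

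A reader might infer that the plan tests a wrong null, that bias is certain, or that false-positive rates can be quoted. The documents do not support this. They state no null hypothesis for healthcare cost, they say only that healthcare use may change, and any rejection rate would rest on an invented REP effect. Nor does comparing the two estimators tell the reader nothing: a gap between them would be a warning.

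**Conclusion.** The concern holds in a limited form. As described, the cost comparison lets sites whose REP status is changing act as controls for CE, so a REP cost effect can leak into the CE estimate. The leak runs from near zero to somewhat under half of REP's effect in the lasting-effect scenarios. Its sign varies with the cohort gap, the shape of the REP effect, the treatment date and the follow-up window, none of which the article gives for costs. Because the two named estimators can err in opposite directions, their agreement is not a reliable check.

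If REP does not change costs there is no leak. The point concerns a secondary economic analysis and leaves the primary reach outcome untouched. It is still worth correcting, because the randomisation already supplies a contrast that needs no assumption about REP's cost effect.

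**What to change.** Make the main REP + CE versus REP cost analysis a within-cohort contrast: site effects plus cohort-by-quarter effects, with a CE indicator from REP month 9 at REP + CE sites. Equivalently, allow only REP sites of the same start cohort as controls. State the treatment date and the follow-up window. Keep the common-time two-way model and the pooled staggered estimator as sensitivity analyses.

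This changes one set of model terms and needs no new data. The price is that each cohort contributes 2 sites against 2. In the simulation the estimator SD rose from 0.37 to 0.42 relative to the two-way model, a ratio of 0.42/0.37 = 1.14, and stayed below the staggered estimator's 0.51.
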